# PORTAL: Pilot study on the safety and tolerance of preoperative melatonin application in patients undergoing major liver resection: a double-blind randomized placebo-controlled trial

**DOI:** 10.1186/1471-2482-8-2

**Published:** 2008-01-23

## Abstract

**Background:**

Major surgical procedures facilitate systemic endotoxinemia and formation of free radicals with subsequent inflammatory changes that can influence the postoperative course. Experimental data suggest that preoperative supraphysiological doses of melatonin, a potent immuno-modulator and antioxidant, would decrease postoperative infectious and non-infectious complications induced by major abdominal surgery.

**Methods/Design:**

A randomized controlled double blind single center clinical trial with two study arms comprising a total of 40 patients has been designed to assess the effects of a single preoperative dose of melatonin before major liver resection. Primary endpoints include the determination of safety and tolerance of the regimen as well as clinical parameters reflecting pathophysiological functions of the liver. Furthermore, data on clinical outcome (infectious and non-infectious complications) will be collected as secondary endpoints to allow a power calculation for a randomized clinical trial aiming at clinical efficacy.

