### Trial rationale

Experimental data suggest that melatonin applied preoperatively would be suitable for prevention or prophylactic treatment of postoperative infectious and non-infectious complications induced by major surgical interventions. Exogenous, intragastrically applied melatonin as well as endogenously generated melatonin has been shown to promote healing of gastric ulcers in rats [23]. This antiulcer activity has been attributed to the ability of melatonin to stimulate enzymes that protect against oxidative stress [24,25]. Besides, orally-administered melatonin has been found efficient in reducing negative parameters of cholestasis and provided a hepatoprotective effect against the liver injury secondary to acute ligation of the biliary duct in rats [26,27]. Most recently we observed that rats gavaged with melatonin 2 h before warm ischemia/partial liver resection survive significantly longer than appropriate controls (unpublished data). Enzymes (transaminases) indicative for liver damage were also significantly reduced after preoperative melatonin following warm ischemia in both rats and pigs in a dose dependent manner (unpublished data). In clinical setting, melatonin has been shown to enhance neutrophil apoptosis after partial hepatectomy causing liver ischemia and reperfusion [28], thus eliminating the consequent active inflammatory response due to surgical injury [29]. Most recently, data from a randomized clinical trial has shown intravenous melatonin to decrease oxidative stress status and proinflammatory cytokines in human neonates undergoing surgery for congenital malformations [30]. However, the best administration route, the duration of treatment, the effective dose of melatonin, its exact role in the pathophysiology of surgical diseases, its pharmacological interactions and untoward side effects, as well as its long-term safety has not been fully established yet. Thus, this study has been designed to meet the need for a larger randomized controlled trial to confirm the suggested benefits of melatonin with the consideration of the current knowledge of its immunomodulatory effects.

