### Objectives and endpoints

The primary aim of this pilot study is to evaluate safety and tolerance of preoperative application of melatonin in patients undergoing operative procedures for partial liver resection. In addition, clinical parameters reflecting pathophysiological functions of the liver will be determined.

Data on clinical outcome (infectious and non-infectious complications) are collected as secondary endpoints to allow a power calculation for a randomized clinical trial aiming at clinical efficacy (Table 2).

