### Randomization and blinding

Randomization (1:1) will be performed by the algorithm programmed in specific computer software and a randomization list will be prepared. Briefly, "blocked randomisation" will be performed using blocks of four that will include equal packages of test product and control product with the order of treatments within a block being randomly permuted, thus ensuring treatment group numbers are evenly balanced at the end of each block. The random number sequence is chosen to start from 1001 and sets an ascending allocation order for the first four subjects. Similarly, treatment type is allocated to the next four patients in the order specified by the next randomly selected permutation. The process is then repeated. The randomization list will be prepared by the institution that is responsible for the packaging of the study products (test product, placebo), i.e. the Pharmacy of the University clinic of Heidelberg, and kept in safe and confidential custody at this institution.

Patients satisfying the enrolment criteria will receive an ascending serial number in the order of their enrolment. Patient numbers for patients who replace drop-outs will be assigned similarly.

Both study products, test (melatonin) and placebo product (microcrystalline cellulose), will be of same form and appearance (white powder in sachets) including the packaging material.

In addition to the trial medication, the clinical trial director (PS) will receive a set of sealed envelopes, one for each randomization number. An identical set of sealed envelopes will be held at the Pharmacy of the University clinic of Heidelberg. These envelopes contain information on the subject's trial medication and are to be opened only under circumstances in which it is medically imperative to know what the subject is receiving.

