### Statistics and data management

All analyses will be carried out on an "intent-to-treat" basis. However, attempts will be made to analyze "per protocol" and "intent-to-treat" populations separately, when statistically appropriate. For the purpose of "per protocol" analysis, two groups of 20 eligible patients completing the protocol will be considered. Drop-out patients are not to be replaced.

The target variables of this trial include laboratory values, outcome parameters and adverse events. The target variables are measured from study day -1 to study day 7. The differences of the laboratory values between study day -1 and 7 are tested with the paired t-test or, in case of uneven distribution, the Wilcoxon-test (2-sided) for within group comparison. The Mann-Whitney U test will be used to detect differences between treatment groups. The following statistical values will be calculated when appropriate: mean, standard deviation, 95%-confidence interval of the mean, minimum, lower quartile, median, upper quartile, maximum, valid number, frequency count, and percentage. The laboratory values will be counted according to their normal ranges (below normal, normal, and above normal). SAS software (Version 8.2) will be used for analysis.

All patient data (clinical and resource use) generated during the study will be recorded on the eCRFs provided by HealthEcon AG, Basel, Switzerland. These forms are specifically designed in Microsoft Office Access (Version: 1.01) to meet the data recording requirements of the clinical study protocol. Corrections of wrong entries will be recorded automatically. In addition, for any correction of data concerning "Adverse Events" or the primary target variable the reason for the correction must be entered. All data will be entered into a central database as recorded.

All data management activities will be done according to the current Standard Operating Procedures (SOPs) of HealthEcon AG.

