## Discussion

This clinical trial particularly demonstrates how a scientific hypothesis has been developed from bench to bedside, with classical chain of investigations from early experimental research to the highest level of evidence, a randomized controlled double blind clinical trial. If previous experimental findings are confirmed by the data of this clinical trial, melatonin would improve the overall outcome after major liver resection.

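### The primary endpoint is described in three ways that do not agree, the stated statistics give no between-arm interval for adverse events, and parts of the text promise more than a 40-patient pilot can show

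*Protocol article*

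**What the plan says.** **Primary endpoint.** The abstract (Methods/Design) states: "Primary endpoints include the determination of safety and tolerance of the regimen as well as clinical parameters reflecting pathophysiological functions of the liver". Objectives and endpoints gives safety and tolerance as the primary aim and continues: "In addition, clinical parameters reflecting pathophysiological functions of the liver will be determined". Statistics and data management requires a documented reason for any correction to adverse-event data "or the primary target variable the reason for the correction must be entered". That variable is in the singular and is not identified anywhere in the article.

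**Variables.** Table 2 has a block headed Safety and Tolerance. It contains adverse events and, below them, liver, kidney, substrate and haematology measurements. None is ranked.

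**Analysis.** Statistics and data management treats laboratory values, outcome parameters and adverse events together as target variables. It plans within-group tests of the change in laboratory values from day -1 to day 7, a Mann-Whitney U test between groups, and a list of summary statistics. The list includes counts and percentages. Its only interval is the 95% interval of a mean.

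**Purpose and conclusions.** The abstract and Objectives and endpoints both say that complications are collected as secondary endpoints so that a later efficacy trial can be sized. Trial rationale, however, says "this study has been designed to meet the need for a larger randomized controlled trial to confirm the suggested benefits of melatonin". The abstract's Discussion paragraph places the trial in a chain of research meant to determine whether melatonin improves general outcome. The main Discussion says that, if the trial data confirm earlier experimental findings, "melatonin would improve the overall outcome after major liver resection".

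**The concern.** A reader cannot tell from this text what the trial's primary result will be. It could be an adverse-event measure, a set of liver tests alongside it, or one variable not yet named. The correction rule cannot be applied to that variable until it is identified. Because the rule mentions adverse events and the primary variable separately, it could even be taken to mean that the primary variable is something other than adverse events.

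The choice affects what is concluded. The tests set out in most detail are for laboratory values. The question the trial is built to answer is how much harm remains compatible with the data, and none of the listed statistics answers it. If 14 unranked liver variables may count as primary, a chance difference in one of them could be presented as a primary result. The rationale and discussion wording would then make it easy to present that result as clinical benefit.

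**Working it through.** **1. The three descriptions side by side**

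| Place | Safety and tolerance | Liver parameters |
|---|---|---|
| Abstract, Methods/Design | primary | primary |
| Objectives and endpoints | primary aim | additional, not called primary |
| Statistics and data management | one primary variable, not named | one primary variable, not named |

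**2. Inputs**
- Sample size: "comprising a total of 40 patients has been designed". Allocation: "Randomization (1:1) will be performed", in blocks of four. 40/4 = 10 complete blocks, so 20 per arm. The per-protocol description agrees: "two groups of 20 eligible patients completing the protocol will be considered".
- Liver variables in Table 2: integrity 6 (AST, AP, GGT, ALT, LDH, GSH) + synthesis 7 (CE, Chol, TP, PT, PTT, albumin, CRP) + elimination 1 (bilirubin) = 14.
- Assumed, because the article does not state them: a two-sided 5% level per test, one between-arm test per variable, and all complication rates in step 5.

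The article gives no power or precision target for 40 patients, so there is no figure of its own to reproduce here.

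**3. False positives among the liver variables, if melatonin affects none of them**
- Expected number = 14 × 0.05 = 0.7. Correlation does not change this.
- Chance of at least one, if independent = 1 − 0.95^14 = 1 − 0.488 = 0.512.
- Liver markers are correlated, so 51% is an upper guide. With normally distributed test statistics and an assumed common correlation of 0.5, numerical integration gives 0.348. At 0.7 it gives 0.249.

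**4. What an interval for adverse events would show**
- Zero events in 20: exact two-sided 95% upper limit = 1 − 0.025^(1/20) = 0.168.
- 0/20 in both arms: the Wilson upper limit per arm is 3.84/(20 + 3.84) = 0.161. The Newcombe 95% interval for the risk difference is therefore −16 to +16 percentage points.
- 6/20 in both arms (illustrative): the Wilson limits are 0.145 and 0.519. The half-width is √[(0.300 − 0.145)² + (0.519 − 0.300)²] = 0.268, so the interval is −27 to +27 points.

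A Mann-Whitney p-value gives none of these figures.

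**5. Whether 20 per arm could confirm a reduction in complications**

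Exact power of Fisher's test, two-sided 5%, summed over all outcomes of two binomials with n = 20. The rates are assumptions that span a range.

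| Assumed rates | Power |
|---|---|
| 20% vs 10% | 7% |
| 30% vs 15% | 12% |
| 40% vs 20% | 19% |
| 50% vs 25% | 27% |

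**6. The Discussion's condition**

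The experimental findings cited in Trial rationale include longer survival in rats and lower transaminases in rats and pigs. The Discussion does not say which of them must be confirmed. A transaminase difference alone could therefore satisfy its condition and lead to the statement about overall outcome.

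**The case against.** The strongest reply is that Table 2 files the liver variables under Safety and Tolerance, and that the adverse-event definition includes changes in laboratory values. On that reading the abstract and the objectives differ more in wording than in design. Screening safety laboratory values without a multiplicity correction is also normal in a pilot, since correction makes harm harder to see. This largely stands. It is why the liver variables should stay as safety measures and why no correction is asked for. It does not settle whether they are primary, and it does not identify the unnamed variable.

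Second, the article condenses a fuller protocol, and an analysis plan could add a risk difference. That is fair and makes this the weakest part of the point. It remains because the article itself lists its statistics and gives an interval only for a mean.

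Four stronger readings may suggest themselves, and the documents do not support them:
- **That adverse events are not compared between arms.** They are among the target variables, a between-group test is named, and counts and percentages are listed. What is missing is an effect size with an interval.
- **That roughly 30 laboratory variables are all primary.** The kidney, substrate and haematology values are nowhere called primary, so only the 14 liver variables enter the calculation.
- **That the plan is committed to concluding improved outcome.** The Discussion sentence is conditional, and the objectives reserve efficacy for a later trial.
- **That low power is itself a defect.** It is acceptable in a pilot. It matters only against wording that speaks of confirming benefit.

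**Conclusion.** The point holds as a problem of consistency and of what may be concluded. The three descriptions of the primary endpoint cannot all be applied as written, and one variable with an operational role is unnamed. The stated between-arm method gives no estimate of the difference in adverse events. The abstract's Discussion paragraph, Trial rationale and the main Discussion go beyond the pilot purpose, the last of these conditionally.

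The size is moderate. If the 14 liver variables were each tested between arms at 5%, 0.7 false positives would be expected. The chance of at least one is 51% under independence and about 25% to 35% at common correlations of 0.7 to 0.5. Even a clean safety result of 0/20 leaves a true rate of 16.8% possible, which is why the interval matters more than a p-value. Under the assumed rates, power to show a halving of complications is 7% to 27%, so clinical benefit could not be confirmed. The significance level, correlations and complication rates are assumptions. The 14 variables and 20 per arm come from the article.

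**What to change.** 1. Align the abstract, Objectives and endpoints, and Statistics and data management on safety and tolerance as primary. The sponsor should name the event-based measure and use the same name in the data-correction rule. Patients with at least one adverse event, or with at least one serious adverse event, are examples; the documents do not dictate either.
2. Report that measure and the complications per arm with exact 95% confidence intervals, and as a between-arm risk difference with a 95% confidence interval.
3. Keep the liver variables as supporting safety measures. Report them as between-arm estimates with confidence intervals, and make no confirmatory claim from an individual p-value.
4. Reword the abstract's Discussion paragraph, Trial rationale and the main Discussion to say that the pilot estimates safety and event rates for planning an efficacy trial and cannot confirm clinical benefit.

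**Cost.** No extra patients, visits or assays. The sponsor gives up claims resting on single laboratory p-values. Enrolment began in June 2007, so the clarification should be recorded and dated before unblinding, to show that it was not driven by the results.

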**Discussion:**

Based on experimental data, this ongoing clinical trial represents an advanced element of the research chain from bench to bedside in order to reach the highest level of evidence-based clinical facts to determine if melatonin can improve the general outcome after liver resection.

**Trial Registration:**

EudraCT200600530815

## Background

Surgical injury triggers a proinflammatory cascade of hormonal, immunologic, and cellular responses collectively known as acute phase response to minimize damage and to hasten healing and recovery as John Hunter once described it as "both the disposition and the means of cure [1]." However, the consequences of this sophisticated sequence of events are not always advantageous for the surgical patient due to the varying magnitude of the response and the severity of the injury. Tissue ischemia and the subsequent reperfusion, particularly in visceral organs, as well as loss of intra- and extravascular volume due to hemorrhage, burn injury or extracorporeal circulation can result in oxidative stress, in both surgical and distant sites, microvascular leakage, platelet aggregation, leukocyte-endothelium adhesion, and depression of humoral and cell-mediated immunity that subsequently lead to proinflammatory changes [2]. Systemic endotoxinemia is accentuated due to the leakage of aerobic and anaerobic microflora from the gastrointestinal tract through microvascular damage resulting from ischemia/reperfusion injury, altered immunity secondary to the inflammatory cascade, visceral ischemia and necrosis, hemorrhage and hypotension [3]. Under these circumstances the occurrence of transient endotoxinemia and formation of free radicals is almost certain with both infectious and non-infectious postoperative complications as possible consequences. Surgical infections, identified as a major limiting factor to the postoperative clinical recovery, do occur in spite of preventive treatment with antibiotics immediately before or during surgical treatment and represent a major challenge especially when more complex and high-risk operations are performed in more debilitated patients, and in the face of increasing antibiotic resistance.

### Melatonin

Melatonin (N-acetyl-5-methoxytryptamine) is a hormonal product primarily produced and secreted by the pineal gland, although it has been detected in other tissues as well [4]. Melatonin is involved in the circadian rhythm and the sleep-wake cycle of vertebrates. In addition to its main function of sleep induction, melatonin is also known for its immunomodulating activities as well as for its antioxidative effects [5-7]. Melatonin is the most powerful endogenous free radical scavenger known at present. It not only directly neutralizes a number of free radicals and reactive oxygen species, but also stimulates several antioxidative enzymes which increase its efficiency as antioxidant.

In terms of direct free radical scavenging, melatonin interacts with the highly toxic hydroxyl radical with a rate constant to that of other highly efficient hydroxyl radical scavengers. Additionally, melatonin reportedly neutralizes hydrogen peroxide, singlet oxygen, peroxynitrite anion, nitric oxide and hypochlorous acid and stimulates antioxidant enzymes such as superoxide dismutase, glutathione peroxidase and glutathione reductase. Melatonin can be widely used as a protective agent against a wide variety of processes and agents that damage tissues via free radical and reactive oxygen mechanisms. The highest concentration of melatonin has been found in the hepatobiliary system [8] with high-affinity binding sites in hepatocyte nuclei [9].

### Pharmacokinetics

The antioxidative effects of melatonin require concentrations that are much higher than endogenously produced plasma concentrations (peak plasma levels of approximately 100 pg/ml) [10]. Exogenous oral doses of melatonin >0.3 mg produce already supraphysiological levels in humans [11]. Orally administered melatonin is subject to extensive first-pass metabolism in the liver, and absolute bioavailability is reported to be approximately 15%, although highly variable [12,13]. Melatonin has an elimination half-life (t_1/2_) of 30–45 min [14-17] which is extended to approximately 100 min in cirrhotic patients [15]. In humans, the principal metabolite of endogenous as well as exogenous melatonin is 6-sulphatoxy melatonin [18].

Toxicity of melatonin is remarkably low. It was not possible to determine DL50 for melatonin since the highest possible does (800 mg/kg BW; limitation imposed by the solubility of the compound) failed to induce mortality in mice [19]. When melatonin was given to rats on gestation days 6–19 in very large doses (50–200 mg/kg BW, the doses equal to ~17.5 – 70 g/day) the maternal toxicity NOAEL (No Observed Adverse Effect Load) and LOAEL (Lowest observed adverse effect level) were 100 and 200 mg/kg/day, respectively, and the developmental toxicity NOAEL was >200 mg/kg BW [20]. No significant adverse effects were observed following administration of high doses (3 – 6.6 g/day) to eleven individuals for 15 to 35 days [21].

In the United States, the Food and Drug Administration (FDA) has designated melatonin as an orphan product sold as a dietetic complement with the only therapeutic indication in circadian rhythm disturbances in blind patients [22]. In most European countries this hormone is considered as a scientifically non-evaluated drug, therefore its sale is not allowed [4].

### Trial rationale

Experimental data suggest that melatonin applied preoperatively would be suitable for prevention or prophylactic treatment of postoperative infectious and non-infectious complications induced by major surgical interventions. Exogenous, intragastrically applied melatonin as well as endogenously generated melatonin has been shown to promote healing of gastric ulcers in rats [23]. This antiulcer activity has been attributed to the ability of melatonin to stimulate enzymes that protect against oxidative stress [24,25]. Besides, orally-administered melatonin has been found efficient in reducing negative parameters of cholestasis and provided a hepatoprotective effect against the liver injury secondary to acute ligation of the biliary duct in rats [26,27]. Most recently we observed that rats gavaged with melatonin 2 h before warm ischemia/partial liver resection survive significantly longer than appropriate controls (unpublished data). Enzymes (transaminases) indicative for liver damage were also significantly reduced after preoperative melatonin following warm ischemia in both rats and pigs in a dose dependent manner (unpublished data). In clinical setting, melatonin has been shown to enhance neutrophil apoptosis after partial hepatectomy causing liver ischemia and reperfusion [28], thus eliminating the consequent active inflammatory response due to surgical injury [29]. Most recently, data from a randomized clinical trial has shown intravenous melatonin to decrease oxidative stress status and proinflammatory cytokines in human neonates undergoing surgery for congenital malformations [30]. However, the best administration route, the duration of treatment, the effective dose of melatonin, its exact role in the pathophysiology of surgical diseases, its pharmacological interactions and untoward side effects, as well as its long-term safety has not been fully established yet. Thus, this study has been designed to meet the need for a larger randomized controlled trial to confirm the suggested benefits of melatonin with the consideration of the current knowledge of its immunomodulatory effects.

